# Acupuncture treatment for carotid atherosclerotic plaques: study protocol for a pilot randomized, single blinded, controlled clinical trial

**DOI:** 10.1186/s13063-020-04709-0

**Published:** 2020-09-07

**Keywords:** Carotid atherosclerosis disease, Cervical atherosclerosis plaque, Acupuncture, Vessel plaque quantification (VPQ)

## Abstract

**Background:**

Carotid atherosclerosis disease (CAD) is generally associated with the occurrence of cardiovascular and cerebrovascular accidents. However, CAD has not been taken seriously enough in the clinic, which, coupled with the single treatment and prevention of CAD, has led to a generally low level of patient compliance. Therefore, acupuncture is expected to be a safe and effective therapy that can be maintained in the long term for patients with CAD. The study objective is to evaluate the efficiency and reliability of acupuncture to relieve CAD and provide a new therapeutic idea for the clinical treatment of CAD.

**Methods:**

This is a three-arm randomized clinical trial in China. Three groups (TA, SA, and MC) will be randomly allocated at a 1:1:1 ratio. The study will enrol 105 cervical atherosclerosis plaque patients in total on a voluntary basis, with 35 patients in each group. The treatment will last for 12 weeks, with two treatments per week for twenty-four treatments in total.

**Results:**

Two 3D ultrasound indicators will be measured as the primary outcomes: the total plaque volume (PV) of the carotid artery on each side and the grey-scale median (GSM). The secondary outcomes will include intima-media thickness (IMT), lipid levels, apolipoprotein A-IV level, platelet count (PLT), fibrinogen (FIB), and platelet aggregation rate (PAR). All the outcomes will be assessed before treatment, after treatment, and after a 12-week follow-up period. This study will utilize per-protocol (PP) and intention-to-treat (ITT) analysis principles.

**Conclusions:**

This trial is to evaluate the efficacy and reliability of acupuncture in relieving carotid atherosclerotic plaques by establishing acupuncture (TA), sham acupuncture (SA), and medication (MC) groups.

**Ethics and dissemination:**

This study was approved by the Institutional Ethics Committee of Guangdong Provincial Hospital of Traditional Chinese Medicine (no. YF2018-107-01). All data and findings will be provided by the principal investigator via email.

**Trial registration:**

ChiCTR, ChiCTR1800019259. Registered on 1 November 2018—retrospectively registered, http://www.chictr.org.cn/index.aspx

## Background

Atherosclerotic disease is a type of disease associated with arthritis, lipids, and other metabolic disorders in the body. Atherosclerotic disease is the main cause of cardiovascular and cerebrovascular diseases. According to research, in 2013 alone, 247.9 people died per 100,000 people due to these diseases, accounting for 28.2% of the total number of deaths [1]. Although the population structure has changed, the mortality rate of cardiovascular and cerebrovascular diseases has decreased by 22% [2]. A study found that one American dies every 1 min and 23 s from this type of disease, and a coronary event occurs every 34 s [3]. A 2009 study reported that the indirect and direct costs of cardiovascular disease and stroke in the USA were as high as $31 billion [4]. A study has counted the disease burden in China from 1990 to 2010. Among them, the main cause of death was stroke, and 1.7 million patients died of stroke in 2010. Ischaemic heart disease ranks second, with 948,700 cases of death from ischaemic heart disease, which both have intricate interactions with atherosclerosis [5].

For treatment, antiplatelet drugs and statins are often used in the clinic. Both antiplatelet drugs and statins can effectively reduce the incidence of cardiovascular and cerebrovascular diseases [6–9]. Additionally, aspirin combined with statins can reduce the incidence of cardiovascular events in patients with diabetes [10].

However, studies have found that antiplatelet drugs are not suitable for drug absorption and can cause gastrointestinal irritation and bleeding [11–13]. A survey found that 7–29% of patients taking statins developed myositis [14].

In a multi-centre study that included 2864 participants, the incidence of intracranial stenoses in patients with acute ischaemic stroke was 46.6%, of which 9.11% of cases were associated with carotid stenosis. Stroke patients with head and neck artery stenosis have more severe symptoms after admission and a higher prevalence of recurrent strokes. Head and neck arterial plaque should be an important intervention target for primary prevention before stroke [15].

Acupuncture is used to improve diseases caused by atherosclerosis; for example, acupuncture is used for rehabilitation after stroke. The curative effects of acupuncture include improved blood flow in the ischaemic area after stroke, anti-apoptosis, and the promotion of the growth of nerve cells. For example, acupuncture may promote the proliferation of neural stem/progenitor cells in response to ischaemia via the Wnt/β-catenin pathway and by modulating retinoic acid expression [16–18]. Recent studies have found that acupuncture relieves angina. The acupuncture points for angina pectoris are bilateral acupoints PC6 and HT5 [19]. Acupuncturists often choose BAIHUI (DU20), YINTANG (EX-HN3), and YANGLINGQUAN (GB34) to treat stroke. Research on the efficacy and mechanism of acupuncture in improving atherosclerotic plaque is still insufficient. Acupuncture is widely used in the rehabilitation treatment of atherosclerotic diseases, but acupuncture is mostly used after cardiovascular and cerebrovascular events occur. The purpose of this study is to provide data support for acupuncture in the treatment of atherosclerotic plaques and to provide a new idea for the early prevention of atherosclerosis.

The main objective is to evaluate the efficiency and reliability of acupuncture to relieve carotid atherosclerotic plaques by establishing TA, SA, and MC groups.

## Methods

### Study design

This is a three-arm randomized, parallel control clinical trial. The study objective is to evaluate the efficiency and reliability of acupuncture to relieve CAD. Three groups will be randomly established at a 1:1:1 ratio, including the TA group (receiving acupuncture therapy), the SA group (receiving sham acupuncture therapy), and the medication group (taking aspirin and statins). The study will enrol 105 individuals in total, 35 individuals in each group. The medication group is set for the positive control to evaluate the difference in the curative effect between acupuncture and drugs. At the same time, sham acupuncture group is set for placebo control to evaluate the clinical efficacy of acupuncture. The flowchart of this protocol can be found in Fig. 1.

**Fig. 1 Fig1:**
[figure not shown]
Diagram of trial design, including patient recruitment, inclusion criteria, randomization, three groups (TA group, SA group, MC group), assessment timepoints, and statistical analysis

### Inclusion criteria

Conformation to the diagnostic criteria according to the Guidelines for Diagnosis and Treatment of Head and Neck Arteriosclerosis in China (2017) [20];No cardio-cerebrovascular diseases history;No vulnerable plaque and plaques on both sides that amount to less than five plaques;Cholesterol from 2.59 to 8.0 mmol/L and triglycerides (TGs) from 1.7 to 10.0 mmol/L;Age from 25 to 70 years old (unrestricted sex);No use of any medicine for atherosclerosis during the last 2 weeks;Agreement to participate the study and signed the informed consent before inclusion.

### Exclusion criteria

Carotid aortic stenosis greater than 50% on any side;Greater than or equal to five plaques on both sides;Body mass index (BMI) ≥ 30; hyperlipidaemia patients with cholesterol greater than 8.00 mmol/L. Triglyceride is greater than 10.0 mmol/L;A history of stroke, myocardial infarction (MI), craniocerebral injury, major surgery, arrhythmia, angina, coagulopathy, thyroid disease, liver and kidney insufficiency, psychiatric disorders, or drug abuse;Presence of more than 4 of the following risk factors: older than 60 years, hypertension, smoking, diabetes, obesity, and low high-density lipoprotein (HDL).

### Dropout criteria

Occurrence of severe cardiovascular and cerebrovascular disease or complications which result in stopping the trial;Patients who have severe adverse reactions after acupuncture and cannot successfully complete the course of treatment;The participant was unable to follow the protocol treatment for personal reasons during the course, or reject to continue the study.

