### Recruitment

We will recruit the participants in the physical examination, cardiovascular, and acupuncture departments of the four branches in Guangzhou. At the same time, participants will be recruited through the Guangzhou Volunteer Recruitment Network Platform.

The team staffs will give proper healthy dietary guidance to all participants during after the whole study period to promote subject retention and complete follow-up, as well as reminding the participants of their treatment or assessment schedule. WeChat group will be forming to all participants to communicate with doctors and report adverse events at any time.

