### Primary outcome

Vessel plaque quantification (VPQ) is preferred for observing plaque morphological characteristics as a non-invasive assessment method [23]. The vessel plaque quantification technique has a substantial advantage over traditional two-dimensional ultrasound, which has been used for vascular event risk prediction. There are two aspects to be measured by the same sonologist: the total PV of the carotid artery on each side and the grey-scale median (GSM), which can indicate the average hardness of plaques proportionally [24, 25]. Both the PV and GSM will be assessed on weeks 0, 12, and 24 on each side.

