### Sample size

This is a three-arm study. In our search for previous studies of the effects of acupuncture on the carotid atherosclerotic plaque, it was found that most of the studies were two-arm studies of acupuncture versus drugs. There is a lack of high-quality clinical research. In addition, the effect of acupuncture exhibits a significant correlation between acupoints. Therefore, it is not appropriate to use the previous acupuncture clinical research literature data to estimate the sample size. Furthermore, this is a pilot study to guide future randomized controlled trials and to test the feasibility of the protocol. Considering that there are many clinical blood tests in the study, we will choose the clinical minimum sample size of 30 individuals for each group to reduce the burden of detection of the subjects. The maximum dropout rate within the intervention is expected to be approximately 15%. The total number of patients needed to be randomized is therefore 105 (35 for each group).

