### Statistical analysis

This study will use per-protocol (PP) and intention-to-treat (ITT) analysis principles. ITT will include all subjects who participated in at least one treatment, including participants who dropped out. Missing data for participants who dropped out will be supplemented with the most recent data. The PP principle will analyse all participants’ data that conform to the study protocol, and those of individuals who did not conform to the protocol will not be included.

The data will be analysed by professional statisticians with SPSS 20.0 software (IBM SPSS Statistics, IBM Corp, Somers, NY, USA). First, we will describe the baseline data, such as age, blood pressure, course of the disease, BMI, and sex, and compare the baseline data between the three groups. The continuous variables will be presented as the mean ± standard deviation (SD), and the categorical variables will be presented as the composition ratio and rate.

Continuous variables that conform to a normal distribution will be analysed by ANOVA, and the non-conforming data will be analysed using the rank sum test. Categorical variables will be analysed using the chi-square (*χ*^2^) test or Fisher’s exact test. The confidence interval (CI) will be estimated at 95%, and the significance level will be set at 0.05. A *P* value < 0.05 will be considered statistically significant. The adverse data will be recorded and analysed for the relationship with acupuncture. We will calculate the dropout rate and analyse the reasons for dropping out.

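### Stopping treatment is classed as dropout, so ITT may use a carried-forward zero change where a scan could have been obtained

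*Protocol article*

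**What the plan says.** The Dropout criteria section has three items. One covers severe cardiovascular or cerebrovascular events that end participation. The other two include treatment stops: "Patients who have severe adverse reactions after acupuncture and cannot successfully complete the course of treatment" and "The participant was unable to follow the protocol treatment for personal reasons during the course, or reject to continue the study". The last joins coming off treatment and refusing the trial in a single item.

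The Statistical analysis section then states "ITT will include all subjects who participated in at least one treatment, including participants who dropped out" and "Missing data for participants who dropped out will be supplemented with the most recent data".

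On timing, the Primary outcome section says "Both the PV and GSM will be assessed on weeks 0, 12, and 24 on each side".

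The Sample size section says "we will choose the clinical minimum sample size of 30 individuals for each group" and "The maximum dropout rate within the intervention is expected to be approximately 15" per cent, and so randomizes 35 per group.

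Four other places bear on the point:
- Recruitment plans dietary guidance and contact "to promote subject retention and complete follow-up, as well as reminding the participants of their treatment or assessment schedule", for participants in general.
- The MC group section says that pill stops are to be recorded, and does not say whether assessment continues.
- Safety assessment says that people who cannot carry on in the study because of adverse events are excluded, without saying from what.
- The section on the basis of treatment sequence selection sets an 80% threshold for compliance.

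**The concern.** Someone who stops needling or tablets can usually still attend an ultrasound, and an ITT analysis needs that scan. The Dropout criteria do not separate this person from one who refuses all further contact. If both are handled as having left, an obtainable result (regression, no change or progression) is replaced by an assumed zero with no spread, on both primary outcomes. A later analysis plan cannot repair this, because a scan that was never requested cannot be recovered.

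Two features suggest that dropouts are expected to leave without an outcome. The sample size is raised from 30 to 35 to cover dropout during the intervention, and Safety assessment speaks of exclusion.

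The arms are also not described alike. The adverse-reaction item names acupuncture only, and there is no matching item for a drug reaction in the MC group.

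Finally, this is a pilot meant to guide later trials. A dropout rate that mixes treatment stops with refusals of assessment is a poor basis for planning outcome loss.

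**Working it through.** **Inputs.** 30 per group before dropout, 15% maximum dropout during the intervention, and 35 per group randomized (Sample size); scans at weeks 0, 12 and 24 (Primary outcome); latest value carried forward for dropouts (Statistical analysis). No PV or GSM means or SDs are given, so results are ratios or SD units of change.

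**1. The plan's own figure.** 30 × 1.15 = 34.5, rounded up to 35 per group, and 3 × 35 = 105, as stated. Dividing instead gives 30 / 0.85 = 35.3, rounded up to 36; the difference does not matter here. Expected dropouts are 0.15 × 35 = 5.25, about 5 per arm, and 35 − 5 = 30.

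**2. Carry-forward on this schedule.** Illustrative baseline of 100:

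| Week 12 | Week 24 | Change at week 12 | Change at week 24 |
|---|---|---|---|
| missing | missing | 0 | 0 |
| missing | 90 | 0 | −10 |
| 95 | missing | −5 | −5 |

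With no scan between weeks 0 and 12, leaving before week 12 fixes the week-12 change at zero. The week-24 change is zero only if that scan is missed as well.

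**3. Upper bound: all 5 of 35 unscanned.** Let d be the imputed share, 5/35 = 0.143.
- Mean factor: 1 − d = 0.857 of the completers' mean.
- SD factor: √[(1 − d) + d(1 − d)k²], where k is mean change divided by SD of change.
- k = 0: √0.857 = 0.926.
- k = 0.5: √(0.857 + 0.143 × 0.857 × 0.25) = √0.888 = 0.942.

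This describes carry-forward for all dropout, whether or not a scan was obtainable.

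**4. The part the dropout definition can affect.** Let r be the number of those 5 who stopped treatment but would have accepted a scan. The article does not give r, so the whole range is shown. The avoidable error in the arm mean is (r/35) × these stoppers' true mean change. If they are scanned, the imputed share becomes (5 − r)/35.

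| r | Avoidable error (× stoppers' mean) | Mean factor after scanning* | SD factor, k = 0 | SD factor, k = 0.5 |
|---|---|---|---|---|
| 0 | 0 | 0.857 | 0.926 | 0.942 |
| 1 | 0.029 | 0.886 | 0.941 | 0.954 |
| 2 | 0.057 | 0.914 | 0.956 | 0.966 |
| 3 | 0.086 | 0.943 | 0.971 | 0.978 |
| 4 | 0.114 | 0.971 | 0.986 | 0.989 |
| 5 | 0.143 | 1 | 1 | 1 |

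*If stoppers change as completers do. The SD factors rest on the same assumption.

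**5. Between arms.** With equal r in two arms, the avoidable error in their difference is (r/35) × (stoppers' mean in A − stoppers' mean in B). It is zero if stoppers change alike in both arms. With unequal unscanned stopping, a difference can arise from carry-forward alone. Assuming 15% against 5% and the same true change of 0.5 SD in both arms, it is 0.5 × (0.15 − 0.05) = 0.05 SD. These rates and this change are assumptions; the article gives none.

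**The case against.** The strongest reply is that the harm rests on silence. Nothing in the article says that stoppers are not scanned. Off-treatment visits are commonly left to the full protocol, and the visit schedule figure is not shown. Parts of the text also lean towards continued assessment: only missing values are filled, so an obtained scan would be used; the per-protocol set and the 80% rule imply that non-adherent participants can stay in with data; MC stoppers are recorded, not removed; and the scans are scheduled with no on-treatment condition. Raising 30 to 35 may be a routine allowance for loss. The 0.857 factor mainly measures carry-forward itself, and r = 5 is implausible because refusers and people with severe vascular events also count as dropouts.

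Much of this stands. It makes the harm conditional, makes the figures in step 3 a ceiling only, and keeps zero within the range. It does not remove the point. The dropout definition is a stated rule, not an omission, and it puts treatment stops in the category that the analysis section expects to have missing data. The retention measures are general, and neither the MC group section nor the 80% rule says that a stopper is still assessed.

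**Conclusion.** The concern holds as a conditional one. The definition merges two states that an ITT analysis needs to keep apart. For anyone handled as having left before week 12, the carry-forward rule makes the week-12 change in PV and GSM exactly zero.

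The avoidable error in an arm mean lies between 0 and 0.143 times the stoppers' true mean change. The top value requires every one of the planned maximum of 5 dropouts per arm to be a willing but unscanned stopper. The error is zero if stoppers are scanned anyway or if all of them refuse. At equal r, the error in a between-arm difference is zero if stoppers change alike in both arms. The week-24 figures match only if that scan is missed too. Absolute units cannot be given.

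Confidence is medium, because actual visit practice for stoppers is not stated. The change should be made: the potential gain concerns both primary outcomes and the cost is small.

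**What to change.** Define two states, identically for TA, SA and MC:

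- **Stopped assigned treatment**, for any reason, including a needle or drug reaction. Record the date and reason, still carry out the week-12 and week-24 ultrasound and blood tests, and use them in the ITT analysis. Judge per-protocol adherence by the existing 80% rule.
- **Withdrew from further assessment.** Only this state counts as dropout. Imputation is then confined to values that are truly missing: those after withdrawal, plus any scan missed without withdrawal, for example through illness, for which the rule should say what is done.

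Reword the Dropout criteria accordingly, bring the MC group and Safety assessment sections into line, and report the two states separately by arm.

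The cost is rewording three sections and some effort to bring stoppers back; the scans and tests are already scheduled for everyone. Early stoppers among the 42 people who had joined by October 2019 (Trial status) may no longer be recoverable. The change does nothing for participants who refuse further assessment.

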### Study setting

The study team will advertise to the public via the advertising department of the Guangdong Provincial Hospital of Chinese Medicine. The treatment will be conducted at the acupuncture clinic of Guangdong Provincial Hospital of Chinese Medicine. The study will enrol 105 individuals in total, with 35 individuals in each group. Patients who are included in the study are required to sign an informed consent form and will participate in the study on a voluntary basis. The schedule of patient enrolment, intervention, and assessment is illustrated in Fig. 2.

**Fig. 2 Fig2:**
[figure not shown]
SPIRIT figure of enrolment, interventions, and assessments. TA, the acupuncture group; MC, the medication group; SA, the sham acupuncture group; PV, the total plaque volume; GSM, the grey-scale median; APO A-IV, apolipoprotein A-IV; PLT, platelet count; FIB, fibrinogen; PAR, platelet aggregation rate; LDL, low-density lipoprotein; TG, triglyceride; HDL, high-density lipoprotein

### Recruitment

We will recruit the participants in the physical examination, cardiovascular, and acupuncture departments of the four branches in Guangzhou. At the same time, participants will be recruited through the Guangzhou Volunteer Recruitment Network Platform.

The team staffs will give proper healthy dietary guidance to all participants during after the whole study period to promote subject retention and complete follow-up, as well as reminding the participants of their treatment or assessment schedule. WeChat group will be forming to all participants to communicate with doctors and report adverse events at any time.

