### Blinding

Because of the characteristics of acupuncture, the acupuncturists in this study cannot be blinded to the assignment, but the participants can be blinded. The treatment, testing, and follow-up of each group will be implemented independently, with no intersection between each group. The sham acupuncture in this study can guarantee a painful effect, similar to acupuncture, but does not penetrate the skin; sham acupuncture will allow for the better blinding of the participants. In addition, participants in the TA and SA groups will be asked three questions at the end of the 12 weeks to test the blinding effect: ‘Do you have confidence in this treatment?’ ‘Would you recommend this therapy to your friends?’ ‘Can you accept this kind of acupuncture?’ The participants will choose ‘Yes’ or ‘No’ to answer the questions. The data will be analysed at the end of the study. If the results are not significant, then it can be concluded that the blinding was sufficient. To ensure the uniformity of ultrasound examination and blood testing, all ultrasound examinations will be completed by a doctor with over 10 years of vascular ultrasound work experience. The Department of Clinical Laboratory of Guangdong Provincial Hospital of Traditional Chinese Medicine is responsible for the whole blood testing process. Both the ultrasound doctor and clinical laboratory will be blinded to the assignment. Collectors and statisticians responsible for collecting data and statistics will be blinded to the assignment.

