### TA group

Before undergoing acupuncture, patients will be asked to lie in the supine position in a quiet environment. First and foremost, the acupuncturist will sterilize his or her fingers and the skin near the acupoints with 0.5% iodine. Then, quick needle insertion will be performed with a stainless steel needle (30 × 25 mm, Huatuo, Suzhou, China) by skilled acupuncturists. The depth of insertion is flexible and depends on the location of the acupoints and the figure of the patient. NEIGUAN (PC6), YANGLINGQUAN (GB34), and RENYING (ST9) will be inserted first, while BAIHUI (DU20) and YINTANG (EX-HN3) will be inserted subsequently. After that, the needle will be twirled gently and retained for 30 min after the arrival of Qi. When withdrawing the needles, acupuncturists will be asked to press the pinholes with cotton swabs for 2 min in case of bleeding, especially for the RENYING (ST9) acupoint.

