### SA group

The environmental requirements, the acupuncture position, and the treatment frequency of the SA group will be consistent with those of the TA group. The protocol uses a specific blunt needle (30 × 25 mm, Huatuo, Suzhou, China). Acupuncturists will immobilize the translucent tube with double-sided adhesive on the same acupoints as those used in the TA group; then, the acupuncturists will pretend to insert the blunt needle through the tube and keep the needle standing vertically. The patients will feel a little stabbing pain; however, they are not likely to know that the needle did not prick their skin. The operational difference between TA and SA is shown as follows in Fig. 4.

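### A WeChat group for all participants, with no split by arm, conflicts on its plain reading with the stated separation of groups and puts TA versus SA participant blinding at risk

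*Protocol article*

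**What the plan says.** **Communication channel.** The Recruitment section provides that "WeChat group will be forming to all participants to communicate with doctors and report adverse events at any time". It does not say that the channel is divided by arm or that posts are visible to staff only.

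**Separation of arms.** The Blinding section states that "the acupuncturists in this study cannot be blinded to the assignment, but the participants can be blinded", and then: "The treatment, testing, and follow-up of each group will be implemented independently, with no intersection between each group".

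**Sham procedure.** Under SA group: "Acupuncturists will immobilize the translucent tube with double-sided adhesive on the same acupoints as those used in the TA group". A blunt needle is then placed through the tube without entering the skin. The Fig. 4 caption counts tube, adhesive and blunt needle as the components of the sham device.

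**Acupuncture procedure.** Under TA group, "quick needle insertion will be performed with a stainless steel needle (30 × 25 mm, Huatuo, Suzhou, China) by skilled acupuncturists"; then "the needle will be twirled gently and retained for 30 min after the arrival of Qi"; and at withdrawal the acupuncturists are to "press the pinholes with cotton swabs for 2 min in case of bleeding", with particular attention to ST9. Neither tube nor adhesive is mentioned.

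**Handling of dropouts.** Under Statistical analysis, the ITT set takes in everyone with at least one treatment, and a dropout's missing values are replaced by that person's latest available values. Outcomes are collected at weeks 0, 12 and 24.

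**The concern.** SA is the placebo control, so TA versus SA is the only comparison in which participant blinding can do any work. The sham depends on participants having nothing to compare their own experience with. A channel open to both needling arms, set up partly for reporting adverse events, invites that comparison. Bleeding and pinhole reactions point to a penetrating needle; a tube stuck to the skin points, on the description given, to the sham.

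Participants who believe they are on sham may change their diet, seek other treatment or leave the study. Any of these would affect lipids, possibly plaque, and the pattern of missing data, and would do so differently in the two arms.

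**Working it through.** No stated figure is in dispute, so the check is mainly a comparison of sections.

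**Step 1: do the two provisions conflict?** Blinding keeps treatment, testing and follow-up apart by arm. Contact with study doctors and adverse-event reporting belong naturally to treatment and follow-up. Recruitment opens both to all participants through a WeChat group. No other section splits the channel. Followed as written, the plan creates a contact point between arms that Blinding says will not exist.

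**Step 2: would shared posts carry information about the arm?**

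| Feature | TA as described | SA as described |
|---|---|---|
| Device at the point | Stainless steel needle; no tube mentioned | Tube fixed with adhesive, blunt needle |
| Skin | Penetrated | Not penetrated |
| Manipulation | Twirling, 30 min retention | Not described |
| Withdrawal | Pinholes pressed for 2 min | Not described |

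The first two rows are differences on the text; the absence of a tube in TA is inferred from the description. In the last two rows the SA entry is silence, not a stated difference. The SA group section itself acknowledges an operational difference and refers to Fig. 4. Safety assessment lists bleeding among the reactions acupuncture may cause, and adverse events are what the channel is meant to collect.

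**Step 3: how many could be reached?** 35 per arm × 2 needling arms = 70 participants, each planned for 24 sessions over 12 weeks. This is an upper bound on access to the channel. It is not a rate of unblinding.

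**Step 4: how would dropout enter the comparison?** With measurements only at weeks 0, 12 and 24, a participant who leaves before week 12 without further measurement has only the baseline value to carry forward and is scored as zero change. Let Δ be the mean change that would have been seen in either arm, assumed equal, and d the fraction leaving before week 12.

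- Imputed arm mean: (1 − d) × Δ
- Spurious TA − SA difference: (1 − d_TA)Δ − (1 − d_SA)Δ = (d_SA − d_TA) × Δ

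If, purely as an illustration, the protocol's 15% maximum dropout occurred in SA and none in TA, the spurious difference would be 0.15 × Δ. If dropout is equal in both arms, it is 0. The document gives neither Δ nor any arm-specific dropout, so this shows the mechanism and does not estimate the bias.

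**Step 5: would the planned blinding check find it?** The three questions put to TA and SA participants at the end of the 12 weeks ask about confidence, recommendation and acceptance. None asks which treatment the participant believes was given, so they would not detect this unblinding directly.

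**The case against.** The strongest reply is that the conflict comes from loose English. The Recruitment sentence does not say that there is one group, or that participants see each other's posts; its stated purpose is contact with doctors. Separate groups per arm, or a channel only doctors can read, would fit the Blinding section. Messaging is also not named among the activities kept apart. This stands as a limit on certainty: a reader might infer a proven shared chat, and the text does not prove it. But the text states neither of the harmless arrangements, and the plain reading is a channel for everyone.

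A reader might also infer that the tube is certainly absent from TA, or that SA omits retention and swab pressing. The first is a reasonable inference from the TA description and the Fig. 4 caption, but the figure is not shown. The second does not follow: a condensed article that is silent on those SA steps has not stated a difference.

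A third tempting reading is that the primary outcomes are compromised at assessment. They are not. The ultrasound doctor, laboratory, data collectors and statisticians are all stated to be blinded. Dietary guidance goes to all participants, and the treatments expressly allowed alongside are those for conditions not closely related to atherosclerosis. These safeguards narrow the harm to behaviour and dropout but do not remove it. The Limitations section itself accepts that diet affects lipid levels.

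Finally, seeing a tube unblinds nobody unless experiences are compared and the participant can tell which procedure is the sham. What participants are told at consent is not available, so the chain is plausible but not demonstrated.

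**Conclusion.** The concern holds as a risk to participant blinding arising from two provisions that need to be reconciled. It rests on two plain-reading assumptions: that the WeChat group is common to the arms, and that TA is given without the tube. If the sponsor already uses separate or doctor-only channels, one sentence saying so settles the matter.

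Up to 70 participants could be reached, but the amount of unblinding and any resulting bias cannot be derived from the document. It would be wrong to infer that all 70 are unblinded. Tablets against needles could not be concealed from participants in the medication (MC) arm, so the point concerns TA versus SA alone. It deserves correction because this is the only placebo-controlled comparison, the planned questions would not reveal the problem directly, and the remedy is nearly free.

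**What to change.** 1. Replace the common group with private messaging between each participant and study staff, with adverse events reported privately. A broadcast-only channel can carry reminders. At minimum, keep separate channels per arm. Contact at any time is preserved.
2. Reconcile the Recruitment and Blinding sections so that the separation of arms expressly covers messaging.
3. State that participant blinding applies to TA versus SA only.
4. Report that participants enrolled before the change may have been exposed. Trial status gives 42 people by October 2019.

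The cost is a little staff time for individual messages, and the change cannot undo exposure that has already occurred. Altering the needling procedures so that the two arms look alike is not recommended at this stage: with 42 people already in the trial, it would create two versions of the intervention within a small arm.
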